## 10. Funding and Justification

|                                                                               | FEC                 | Funded amount (GBP) | Funded amount (MKW)       |
|-------------------------------------------------------------------------------|---------------------|---------------------|---------------------------|
| Malawi-Liverpool-Wellcome Trust:                                              |                     |                     |                           |
| DIRECTLY INCURRED COSTS                                                       |                     |                     |                           |
| Staff                                                                         | £ 38,977.77         | £ 38,977.77         | 39,407,152.13 MWK         |
| Lab Consumables (including storage of samples)                                | £ 22,308.53         | £ 22,308.53         | 22,554,282.49 MWK         |
| Clinic Consumables (including stationary, clinic expenses and shipping costs) | £ 3,726.00          | £ 3,726.00          | 3,767,045.90 MWK          |
| IMP                                                                           | £ 500.00            | £ 500.00            | 505,508.04 MWK            |
| Staff Miscellaneous                                                           | £ 1,300.00          | £ 1,300.00          | 1,314,320.90 MWK          |
| Research Support                                                              | £ 15,400.00         | £ 15,400.00         | 15569647.59 MWK           |
| Patient reimbursement on day 28 FU                                            | £240                | £240                | 242643.86 MWK             |
| Ethics and Regulation Fees                                                    | £ 10,860.00         | £ 10,860.00         | 10,979,634.60 MWK         |
|                                                                               |                     |                     |                           |
| INDIRECT COSTS                                                                | £ 6,772.00          | £ 6,772.00          | 6,846,600.90 MWK          |
| Sub – Total                                                            | £ 100,084.30 | £ 100,084.30 | 101,186,836.40 MWK |
|                                                                               |                     |                     |                           |
| TOTAL funded by MRC                                                    | £ 112,472.41 | £ 109,995.40 | 111,207,117.85 MWK |

Converted using [https://ec.europa.eu/info/funding-tenders/how-eu-funding-works/information-contractors-and-beneficiaries/exchange-rate-infoeuro\\_en](https://ec.europa.eu/info/funding-tenders/how-eu-funding-works/information-contractors-and-beneficiaries/exchange-rate-infoeuro_en)

Rates as of December 2020 £1= 1011.01608MWK

| Cost                           | Justification                                                                                                                                                                                                                                                                           |
|--------------------------------|-----------------------------------------------------------------------------------------------------------------------------------------------------------------------------------------------------------------------------------------------------------------------------------------|
| Staff –directly incurred Posts | One and a half midwives in Malawi will be necessary to consent and recruit women and to administer the intervention to women and to infants. The study will recruit over 6 months. We will employ midwives for 9 months to allow for training and for any necessary follow up following |

|                               |                                                                                                                                                                                                                                                                                                                                                                                                                                                                                                                                                                                                                                                                                                                                                                                                                                                                                                                                                                                                                                                                                                                                                                                                                                                                               |
|-------------------------------|-------------------------------------------------------------------------------------------------------------------------------------------------------------------------------------------------------------------------------------------------------------------------------------------------------------------------------------------------------------------------------------------------------------------------------------------------------------------------------------------------------------------------------------------------------------------------------------------------------------------------------------------------------------------------------------------------------------------------------------------------------------------------------------------------------------------------------------------------------------------------------------------------------------------------------------------------------------------------------------------------------------------------------------------------------------------------------------------------------------------------------------------------------------------------------------------------------------------------------------------------------------------------------|
|                               | 
study completion, (£14.6K). The laboratory work for this study will all be done in Malawi. The primary end-point for this study is microbiological in nature and this requires intensive microbiology work. A full-time laboratory technician will be employed for 9 months to undertake this work, (£10.5K). This study is a clinical trial of two intervention agents which will need preparation as investigational medicinal products (IMP). This will require support from clinical trials pharmacy and this study will contribute 15% FTE of a pharmacist to support this, (£5K). The majority of the data management will occur at the Malawi Liverpool Wellcome Trust and data management time is included in the directly incurred costs from Malawi. Data management and project management at St George's, University of London (SGUL) will be given in-kind.
                                                                                                                                                                                                                                                                                                                                                                                               |
| Staff –directly allocated     | 
This is a pilot study with limited resources, and so directly allocated costs have been minimised with a substantial amount of work being given to this study in-kind. Dedicated time has been allocated for the Principle Investigator and local study Co-Investigators to provide oversight to the study. Specifically [name] (0.01FTE) will provide overall oversight for the study. [name] will co-ordinate the study. [name] from MRC-Clinical Trials Unit at University College London (MRC-CTU/UCL) will give her contribution in-kind. To deliver the statistical analysis required by this study 2.5% FTE salary contribution will be made to [name], a statistician at the MRC-CTU/UCL. She will provide support with analysis and interpretation of the results. [name] (0.026FTE) from Liverpool School of Tropical Medicine (LSTM) will support the microbiology within Malawi. [name] (0.01FTE) from University of Liverpool will provide obstetric expertise. This will be supported by [name] (0.02FTE) in Malawi. [name] (0.05FTE) will provide neonatal and paediatric oversight in Malawi. [name] (0.05FTE) in Malawi will lead the qualitative components, (£8.3K).
 |
| Other directly incurred costs | 
Consumables will be required to recruit participants, prepare the interventional product, administer interventional agents, collect swabs and to conduct the microbiological analysis required. These include paper and stationary, containers, aprons, sterile gloves, swabs, agar plates and media and inoculation loops. Chlorhexidine will be procured in-country. Octenidine Phenoxylethanol will be supplied from the manufacturer. Shipping for consumables has been included in the budget. Research consumables are estimated at £26,000. This study will be managed as a clinical trial and costs for the appropriate approvals and data management are incorporated (approximately £28,300). Patient reimbursement for day 28 follow up visit will be provided as a flat rate, £1.20 per patient and £240 in total.
                                                                                                                                                                                                                                                                                                                                                                                                                                         |
| Estates and indirect costs    | 
The estate and indirect costs have been included for staff at SGUL, LSTM, University of Liverpool and MRC-CTU/UCL, (£4K). The indirect and overhead costs have also been included at 10% for University of Malawi, College of Medicine, (£6.7K).
                                                                                                                                                                                                                                                                                                                                                                                                                                                                                                                                                                                                                                                                                                                                                                                                                                                                                                                                                                                                                       |

## Revision History

| Version   | Author | Date       | Reason for Revision                                                                                                                                    |
|-----------|--------|------------|--------------------------------------------------------------------------------------------------------------------------------------------------------|
| Draft 0.1 | MC     | 02/02/2022 | First draft – copy of protocol version 3.0                                                                                                             |
| Draft 0.2 | MC     | 12/08/2022 | First substantial draft                                                                                                                                |
| Draft 0.3 | MC     | 12/09/2022 | Updated after comments from SW                                                                                                                         |
| Draft 0.4 | MC     | 21/09/2022 | Updated with subgroups following discussion in TMG                                                                                                     |
| Draft 0.5 | MC     | 04/10/2022 | Updated following comments from [name]                                                                                                        |
| Draft 0.6 | MC     | 22/02/2023 | Updated following comments from [name] and [name] and following interim analyses of safety data (see interim analysis section below) |
| Draft 0.7 | MC     | 13/04/2023 | Updated with prior information for Bayesian analysis                                                                                                   |
| Draft 0.8 | MC     | 24/04/2023 | Updated after comments by EB                                                                                                                           |
| V1.0      | MC     | 10/05/2023 | Updated after final comments by JC and upversioned                                                                                                     |

## 1. Trial design

### 1.1. Design & outline

NeoVT-AMR is a randomised controlled factorial trial with 3x2 + standard of care (SOC) design with two independent strata – labouring mothers and hospitalised neonates. Within each stratum, 147 individuals will be recruited – 21 per treatment combination or SOC. Additionally, 147 babies from mothers in the maternal stratum will also be swabbed at birth.

The two factors are:

- Antiseptic: 1% chlorhexidine (CHG), 2% CHG and octenisept (OCT)
- Frequency of application: once only and multiple applications

Multiple applications timings are 0/4/8/24/28/32h in maternal strata and 0/1/2/3d in neonatal strata.

The SOC group will receive standard of care. For analyses, the reference arm will be 1% CHG once only as there are more effective replicates of each of the factorial arms and therefore greater power for comparison than with SOC. 1% CHG once only was selected as it would be the most straightforward to implement and CHG is more widely available than OCT so evidence of superiority of OCT over CHG would have to be shown for implementation to be advised.

The trial design is summarised in the trial scheme below. Note that the ‘once only’ frequency boxes are (n=21) also.

[figure not shown]

## 1.2. Population

Eligibility to the trial is based on the participant meeting all of the inclusion criteria and none of the exclusion criteria.

### Inclusion criteria

#### Maternal strata

1. Presenting in labour with or without rupture of membranes

#### Neonatal strata

1. Born in a healthcare facility
2. Postnatal age at randomisation <24 hours
3. Birth weight >1000g

### Exclusion criteria

#### Maternal strata

1. Under the age of 18 (minor in Malawi)
2. Any contra-indication to digital vaginal examination
3. In active labour (regular contractions and/or cervical dilatation of more than 4cm)
4. Poor perineal and vaginal skin condition as judged by clinician
5. Planned elective caesarean-section delivery
6. Known or suspected allergy to chlorhexidine or octenidine or phenoxyethanol
7. Intrauterine death confirmed or expected before randomisation
8. Antiseptic application or enrolment in the trial determined inappropriate in the opinion of the enrolling clinician
9. Any recent or planned (within 4 hours) iodine application to the perineum or vagina
10. Unable to obtain consent

#### Neonatal strata

1. Born by planned elective caesarean section
2. Born to mothers recruited in the trial
3. Poor skin condition (skin score of 2 or more in any of three domains (see [Appendix I](#))) at the time of enrolment
4. Known congenital or acquired skin disorder or defect at time of enrolment
5. Antiseptic application or enrolment in the trial determined inappropriate in the opinion of the enrolling clinician
6. Any recent or planned (within 4 hours) iodine application to body
7. Any planned or previous lumbar puncture
8. Unable to obtain parental or guardian consent

The primary analysis population is intention-to-treat, including all randomised babies, regardless of treatment received. This corresponds to estimating the impact of the effectiveness of the treatments. However, in secondary analyses we will also use inverse-probability weighting methods to adjust for deviation from randomised strategy if non-compliance rates are >15%, which is a more efficient approach than defining a per-protocol population (1).

Loss-to-follow rates are unknown but may be high as participants may give birth (in the maternal strata) or be discharged (in the neonatal strata) before all planned swabs are taken. Missing swabs

will be monitored and participants without baseline and two post-baseline swabs may be replaced to maintain power. However, all baseline and post-baseline results will be included in analyses.

## **2. Outcome Measures**

### **2.1. Co-Primary Outcome Measures**

#### **Maternal strata**

- Change in vaginal and perineal bacterial load (in colony forming units)

#### **Neonatal strata**

- Change in neonatal skin bacterial load (in colony forming units)

Bacterial load will be assessed from vaginal and perineal swabs taken separately in the maternal strata and from neck and perirectal swabs taken separately in the neonatal strata. The log CFU for each swab will be summed to get the total log CFU. Timings of the swabs are the same as the timings for applications in the multiple application arm. Swabs are taken before antiseptic is applied.

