## 4.5. Sample Size

The two independent strata each have a factorial design, with an additional control group. Within each stratum, 147 individuals will be recruited – 21 per treatment combination or control. Additionally, 147 babies from mothers in the maternal stratum will also be swabbed at birth.

Recruitment feasibility has been taken into account during the writing of this protocol. Recent audit data (August 2020 – January 2021) in Zomba Central Hospital showed that there were an average of 138 births a week, which is equal to an average of 19 births per day. Rates of caesarean section ranged from 19% to 52%. This indicates that recruitment will be feasible in around 12 months.

The primary endpoints of log colony forming units (CFUs) are widely accepted to be normally distributed. Although all-cause mortality is more relevant, and will be used in the planned future trial, it is not feasible for this pilot due the increased sample size requirements with a binary outcome. High bacterial load (reflected by log CFUs) is associated with increased risk of neonatal sepsis and consequently provides a good balance between relevance to the scientific question and power in a pilot trial.

However, there is very little data on bacterial load in neonates in LMICs. Additionally, bacterial loads are expected to differ across locations complicating interpretation of previous studies. For example, previous studies in neonates have found varying effects of CHG on log colony counts: a decrease from baseline to 24h of 0.2 SD with 1% CHG in Nepal(29) and 2SDs with 2% CHG in the USA(30). Sample size calculations used standard formula with Bonferroni adjustment for multiple testing within arms of frequency and antiseptic. Within each stratum, 147 individuals randomized to 7 treatment groups, 21 participants per group, provides 90% power to detect a difference of 0.82 standard deviations (SDs) between antiseptics (two-sided  $\alpha=0.012$ ) and 0.58 SDs between frequencies ( $\alpha=0.05$ ) (80% power for 0.72 and 0.50 SDs, respectively). This also provides 90% power to detect a difference of 1.01 SD between each antiseptic and control ( $\alpha=0.012$ ), and 0.90 SD between frequency and control ( $\alpha=0.025$ ) (0.88 and 0.79 SDs at 80% power). These expected effects were judged by clinical and statistical members of the team to be sufficient for selecting a treatment regimen for a future trial.

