## **2.4. Sample Size Calculation**

There is very little data on bacterial load in neonates in LMICs. Additionally, bacterial loads are expected to differ across locations complicating interpretation of previous studies. For example, previous studies in neonates have found varying effects of CHG on log colony counts: a decrease from baseline to 24h of 0.2 SD with 1% CHG in Nepal (2) and 2SDs with 2% CHG in the USA (3). The primary endpoints of log colony forming units (CFUs) are widely accepted to be normally distributed. Sample size calculations used standard formula with Bonferroni adjustment for multiple testing within arms of frequency and antiseptic. Within each stratum, 147 individuals randomized to 7 treatment groups, 21 participants per group, provides 90% power to detect a difference of 0.82 standard deviations (SDs) between antiseptics (two-sided  $\alpha=0.012$ ) and 0.58 SDs between frequencies ( $\alpha=0.05$ ) (80% power for 0.72 and 0.50 SDs, respectively). This also provides 90% power to detect a difference of 1.01 SD between each antiseptic and SOC ( $\alpha=0.012$ ), and 0.90 SD between frequency and SOC ( $\alpha=0.025$ ) (0.88 and 0.79 SDs at 80% power). These expected effects were judged by clinical and statistical members of the team to be sufficient for selecting a treatment regimen for a future trial.

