## **2.6. Estimands**

The intervention is the randomised antiseptic and frequency of application.

The patient population is labouring mothers and new-born babies, with birth weight over 1kg admitted to hospital, as defined by the inclusion and exclusion criteria.

The co-primary endpoints are change in skin bacterial colony load, taken from vaginal and perineal swabs in the maternal strata and neck and perirectal swabs in the neonatal strata.

The population-level summary which provides a basis for comparison between treatment conditions is the difference in mean log colony forming units adjusted for baseline value.

Anticipated intercurrent events and associated strategy are:

- Loss to follow-up: rates are unknown but may be high as not many women are anticipated to labour for 32h. The mixed model gives valid estimates assuming outcomes are missing at random.
- Deviation from randomised strategy (antiseptic application and frequency as per protocol) will be assessed using multiple sensitivity analyses:
  - sensitivity analysis will censor at deviation from randomised strategy. Estimated treatment effects will then correspond to the (hypothetical) setting of no deviation.
  - sensitivity analysis using (a) post-intercurrent event data where appropriate and (b) MI will be used to assess robustness of treatment effect inferences where rates of deviation from protocol are above 15%.
  - sensitivity analysis using Inverse-probability weighting methods to adjust for deviation from randomised strategy if deviation rates are above 15%.

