#### Primary analysis

- The primary analysis population is intention-to-treat, including all randomised participants, regardless of treatment received.
- The outcome variable will be change in Total log10 CFU from baseline to assessment time point.
- The primary analysis will include all randomised participants with baseline and at least one post-baseline measure.
- The dependent variable will be total log CFU.
- The model will be a mixed effects model
- Fixed effects in the model will be:
  - Antiseptic (1% CHG, 2% CHG, OCT)
  - Frequency of application (once, multiple)
  - Time point of assessment: hour of swab (continuous; mfp will be used to assess linearity)
  - Baseline total CFU (continuous; mfp will be used to assess linearity)
- Individual will be fitted as a random effect to account for repeated measures within individuals. Goodness of fit of an unstructured covariance matrix will be assessed and used if it is clearly a better fit to the data than random intercepts only.
- Goodness of fit of an interaction between baseline total CFU and timepoint of assessment will be assessed and included in the model if clearly a better fit.
- Normally distributed errors will be fitted.
- The intercept (reference treatment category) will be once only 1% CHG as this is the lowest concentration of CHG, which is believed to be more readily available than OCT, and so would be the most straightforward to implement. The standard of care control will not be used as the reference as the sample size for this arm is lower than for the factorial arms and so power for comparisons is correspondingly lower.
- Comparison of effects between factorial arms will be assessed by testing whether the null hypothesis of no treatment effect can be rejected (equivalent to using the estimate and 95% confidence interval of the estimate of the difference to the intercept).
- Comparisons between other arms and between arms and the SOC arm may also be performed. There will be no formal correction for multiple testing but interpretation will take multiple testing into consideration.
- Model fitting will use restricted maximum likelihood (REML) and p-values are derived using the Kenward-Roger approximation.

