**Repeated samples efficacy sensitivity analysis**

- Change from baseline to the:
  - first outcome measure after baseline
  - final outcome measure
 will also be modelled
- Model and reporting of results will be as the primary analysis except individual will not be fitted as a random effect (as there will be no repeated measures within individuals)

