**Time since antiseptic efficacy sensitivity analysis**

- The primary analysis described above will be repeated with time since last antiseptic application fitted as a fixed effect (continuous; mfp will be used to assess linearity)

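### The primary frequency effect is averaged over a first post-baseline swab at which single and multiple arms cannot differ, so it is attenuated, and the 90% power is not assured when follow-up is short

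*Protocol*

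**What the plan says.** - **Order of swab and application.** SAP 2.1: "Timings of the swabs are the same as the timings for applications in the multiple application arm. Swabs are taken before antiseptic is applied". Protocol 4.7.1.1 (mothers) and 4.7.1.2 (neonates) agree: in the multiple arms each application follows that visit's swab.
- **Times.** SAP 1.1 and 3.2 give 0/4/8/24/28/32 h in mothers and days 0/1/2/3 in neonates. That is five and three post-baseline swabs.
- **Primary model.** SAP 4.6 lists "Frequency of application (once, multiple") among the fixed effects, beside antiseptic, hour of swab and baseline CFU, with a random effect for individual. It has no frequency-by-time term. A baseline and one post-baseline swab are enough to enter.
- **Follow-up.** SAP 2.6 says that loss to follow-up "may be high as not many women are anticipated to labour for 32h". SAP 1.2 expects births and discharges before all swabs are taken. Participants without a baseline and two post-baseline swabs may be replaced, but their data stay in.
- **Power.** Protocol 4.5 and SAP 2.4 claim 90% power for "0.58 SDs between frequencies" at two-sided 0.05 (80% for 0.50 SD). They do not say to which swab, or average of swabs, the difference refers.
- **Other analyses in SAP 4.6.** A separate frequency-by-timepoint model; change to the "first outcome measure after baseline" and to the final measure; and the primary analysis, which "will be repeated with time since last antiseptic application fitted as a fixed effect".

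**The concern.** At the first post-baseline swab the expected difference between frequencies is zero by design. A single frequency coefficient blends this known zero with the later swabs, where repetition can act. The earlier participants give birth or are discharged, the larger the share of the zero.

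Frequency is one of the two factors on which the pilot is to choose a regimen. SAP section 4 says that results will be read from estimates and intervals rather than from significance calls, so an estimate that is too small matters even where power is adequate. It makes repeat application look less useful than it is, by an amount that depends on length of stay or labour.

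**Working it through.** **Inputs from the documents.** 3 antiseptics x 21 = 63 participants per frequency level in each stratum; 0.58 SD; two-sided alpha 0.05; three (neonates) or five (mothers) post-baseline swabs; baseline adjustment.

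**Assumptions, because the documents give no figures.** SD 1 per swab. Exchangeable correlation rho of 0.3-0.7 between all swabs, including baseline. An effect of 0.58 SD from the second post-baseline swab on, and zero before. Time fitted as categories, as an approximation to the planned continuous hour. Early-exit patterns: neonates 30/30/40% with 1/2/3 post-baseline swabs; mothers 30/40/30% with 1/2/5.

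**Step 1: the plan's own figure.** SE = sqrt(2/63) = 0.178. Power = Phi(0.58/0.178 - 1.96) = 90.2%; for 0.50 SD it is 80.1%. Both are reproduced. This is a single-measure comparison without repeated swabs, baseline adjustment or drop-out.

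**Step 2: attenuation with complete swabs.** With k post-baseline swabs the main effect recovers (k-1)/k of the later effect:
- neonates, k = 3: 2/3, so 0.58 becomes 0.387 SD;
- mothers, k = 5: 4/5, so 0.58 becomes 0.464 SD.

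For the average itself to be 0.58 SD, the later effect would have to be 0.58/(2/3) = 0.87 SD in neonates or 0.58/0.8 = 0.725 SD in mothers.

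**Step 3: power of the planned model, complete swabs.** The baseline-adjusted variance of a participant's mean is v(k) = (1 + (k-1)rho)/k - rho^2. At rho = 0.5:
- neonates: v = 0.417, SE = sqrt(2 x 0.417/63) = 0.115, power = Phi(0.387/0.115 - 1.96) = 92%;
- mothers: v = 0.35, SE = 0.105, power = Phi(0.464/0.105 - 1.96) = 99%.

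**Step 4: early exit.** Participants are combined with weights share/v(k). At rho = 0.5, v(1) = 0.75, v(2) = 0.50, v(3) = 0.417 and v(5) = 0.35.
- Neonates: weights 0.40 + 0.60 + 0.96 = 1.96. Share recovered = (0 + 0.60 x 1/2 + 0.96 x 2/3)/1.96 = 0.48. SE = sqrt(2/(63 x 1.96)) = 0.127. Power = Phi(0.278/0.127 - 1.96) = 59%.
- Mothers: weights 0.40 + 0.80 + 0.857 = 2.057. Share recovered = (0 + 0.80 x 1/2 + 0.857 x 4/5)/2.057 = 0.53. SE = 0.124. Power = 69%.

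**Step 5: range over rho 0.3-0.7, with baseline adjustment.** In the last column the frequency term is limited to the second post-baseline swab onward and the first swabs stay in the model.

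| Pattern | Share of effect | Power as planned | Power, restricted term |
|---|---|---|---|
| Neonates, all 3 swabs | 67% | 90-97% | 99% or more |
| Mothers, all 5 swabs | 80% | 99% or more | 99% or more |
| Neonates 30/30/40% | 47-49% | 57-71% | 93% or more |
| Mothers 30/40/30% | 51-55% | 69-80% | 97% or more |

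Without baseline adjustment the early-exit shares are 44-48% and 47-53%, so 44-55% covers both versions.

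**Step 6: the sensitivity analyses.**
- *First outcome measure.* The frequency contrast is zero by design in both strata.
- *Final outcome measure.* This is free of the null swab only for participants with two or more swabs. With 30% holding one swab, about 1 - 0.30 = 70% of the effect remains.
- *Time since last application, neonates.* The covariate is 24 h throughout in the multiple arm and equals hour of swab in the single arm. With hour also in the model, the frequency coefficient becomes the fitted contrast at 24 h, the null swab. A least-squares projection gives 0 for an effect that grows linearly and 0.17 of a step effect.
- *Time since last application, mothers.* The intervals in the multiple arm are 4/4/16/4/4 h, and the same unweighted projection returns about 0.59 of a step effect. The degeneracy is neonatal only.

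**The case against.** Four points have weight.

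1. **Power.** A reader might infer that the 90% is simply lost. The documents do not support that. The stated figure ignores the precision gained from repeated swabs and baseline adjustment, and with complete swabs that gain offsets the dilution. The shortfall appears only with early exit, which the SAP thinks possible but does not quantify.

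2. **Mitigation.** Replacement of participants without two post-baseline swabs (SAP 1.2) and extra recruitment for missing swabs (Protocol 4.7.1.1) would add informative participants. The frequency-by-timepoint model, the final-measure analysis and the summaries at each time point would let the team see a late divergence. This stands, but replacement is optional, and none of it changes the primary estimate. A participant with exactly two post-baseline swabs still carries half the effect.

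3. **Estimand.** A woman who gives birth before a second application gains nothing from a repeat strategy, and under intention-to-treat that belongs to the strategy's effectiveness. Read as an average over swabs, the 0.58 SD power also stands. But SAP 2.6 does not name such an average as the target. The model also puts the null swab into the average for participants who do go on to repeat applications, with weights set by swab counts.

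4. **Selection.** A reader might infer that restricting the contrast adds no selection because the arms are treated alike beforehand. That holds only up to the first post-baseline swab. Later swabs are observed after the arms diverge, in an open-label trial, so validity rests on missing at random, as it does for the current plan.

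**Conclusion.** The concern holds for the estimate and conditionally for power. The equality of the arms at the first swab follows from the schedule and needs no assumption. The 67% and 80% follow from the swab counts if the effect starts in full after the second application. The early-exit figures rest on assumed swab counts and correlation.

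A reader might infer that the analysis favours single application whatever the truth. It does not: attenuation shrinks a real effect, does not reverse it, and leaves a true zero at zero. The supported statement is that the primary frequency estimate is too small by construction, and that the stated 90% is not assured when many participants leave after one or two post-baseline swabs.

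**What to change.** 1. In SAP 4.6, replace the frequency main effect by frequency x (swab after the second scheduled application), that is, from 8 h in mothers and from 48 h in neonates. Keep the first post-baseline swabs for the antiseptic and SOC contrasts.
2. State that this contrast relies on the missing-at-random assumption already made in SAP 2.6.
3. Do not interpret a frequency effect in the first-outcome-measure analysis in either stratum, nor in the neonatal time-since-last-application analysis.
4. In Protocol 4.5 and SAP 2.4, state that 0.58 and 0.50 SD refer to the difference after the second application, and that the power depends on how many participants have such a swab.

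The cost is SAP wording and one model term, with no new data or visits. The downside is that precision depends on how many participants reach the second post-baseline swab. In a harsher assumed neonatal pattern (50/30/20% with 1/2/3 swabs, rho 0.2-0.7), dropping the first swab from the contrast gives 76-94% power, against 33-42% as planned: better, but not always 90%.
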